### 1.2 Surgery with External Beam Radiotherapy

For patients with localized STS amenable to resection with curative intent, surgical treatment in combination with RT results in local disease control in 76% to 92% of patients with successful limb preservation, i.e. avoidance of amputation, in 90 to 95% of patients whose tumors are located on the extremity. Although function-sparing surgery combined with RT represents a significant advance for patients with STS, this approach still requires total en bloc excision of the primary tumor with a goal of 2 centimeters of normal tissue around the tumor in all directions. These operations risk significant morbidity for the patient.

An important component of local therapy in STS is adjuvant RT. Adjuvant RT for patients with STS of the extremity has been shown to reduce local recurrence rates by 20 to 25% relative to radical resection alone. The timing of RT administration (preoperative versus postoperative) has been compared in a randomized clinical trial. This trial demonstrated that preoperative RT was associated with a statistically significant increase in perioperative wound complications (35% vs. 17%). Conversely, at a median follow-up of 6.9 years, preoperative RT was associated with a statistically significant decrease in long term complications, such as joint fibrosis, joint stiffness, and extremity edema (23% vs. 36%). Although these data have been interpreted in different ways by different investigators, advocates of preoperative radiotherapy maintain that the data favor the preoperative administration of RT since perioperative wound complications are generally reversible whereas late complications of radiotherapy are generally irreversible. Furthermore, although considered a secondary endpoint of the trial, overall survival was statistically improved in the patients who received preoperative radiotherapy (85% vs. 75% at 3 years,  $P=0.048$ ). Although these secondary survival data regarding neoadjuvant RT should be viewed with caution, it is reasonable to hypothesize that neoadjuvant RT in combination with novel systemic agents may improve both local and distant disease-control in patients with STS.

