## 7.0 TREATMENT PLAN

### 7.1 Sorafenib Dose Levels and Definition of Dose-Limiting Toxicity

Evaluation for loco-regional toxicity from therapy will occur daily (excluding weekends and holidays) while patient is receiving RT (**see section 10.1 for study calendar**) and then biweekly during the rest period following completion of RT prior to surgical resection. Evaluation for generalized/systemic toxicity (e.g. hypertension, myelosuppression, etc.) will occur weekly (**see section 10.1 for study calendar**) during the treatment phase and then biweekly during the rest phase of the study. Patients will maintain a pill diary so that a record of self-administered medications will be available.

| Dose Level | Sorafenib          | Radiation       |
|-------------------|---------------------------|------------------------|
| 1                 | 200 mg twice daily        | 200 cGy x 25 fractions |
| 2                 | 200 mg q am
400mg q pm | 200cGy x 25 fractions  |
| 2                 | 400 mg twice daily        | 200 cGy x 25 fractions |

A traditional dose-escalation design will be used to determine the MTD of sorafenib combined with radiotherapy. The MTD is defined as the dose that produces dose limiting toxicity (DLT) in 33% of patients. Three patients will be enrolled per dose level, with escalation to the next dose level if no dose-limiting toxicity (DLT) is observed. If one DLT is observed, the dose level will be expanded to a total of 6 patients, and escalation will occur if no more than one DLT is observed among the 6 patients. If 2 or more out of 3 patients, or 3

or more out of 6 patients experience DLT, the study will be terminated or dose reduced to the previous dose level. Dose level escalation will be determined based on DLTs observed from start of treatment until date of surgery, but DLTs will be monitored in the postoperative period, and dose de-escalation may occur if excess late DLTs are observed.

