DLT is defined as: grade 4 anemia, grade 4 neutropenia lasting > 7 days, grade 3-4 thrombocytopenia with clinically significant bleeding or grade 4 thrombocytopenia lasting > 5 days, and grade 3-4 non hematologic toxicity (except: nausea/vomiting that responds to anti-emetic therapy; grade 3 neutropenic fever lasting  $\leq 5$  days; grade 3 encephalopathy lasting  $\leq 2$  days; grade 3-4 hypokalemia, hypophosphatemia, hypomagnesemia, hypocalcemia unless requiring hospitalization; grade 3 diarrhea controlled with medication within 2 days; and grade 3 grade hypertension that is adequately controlled with medication (BP <150/100)).

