#### Treatment Stop Rule

Furthermore, a pause in study accrual will be implemented in the phase II portion of the trial after 10 patients have completed concurrent sorafenib plus conformal radiotherapy followed by surgical resection. Safety assessment will be made 6 weeks following resection of the 10th patient (9 – 13 weeks following completion of concurrent sorafenib and RT) to ensure that excess DLTs are not observed. The study will be ***terminated for safety*** (not lack of efficacy) if 4 of these 10 patients experience grade 3 adverse events or greater since this would represent an increase from the baseline rate of serious AEs expected from the standard combination therapy of preoperative radiation and surgical resection. This pause in accrual will allow us to review all safety data collected to date. If DLTs in excess of our stopping rule are not observed, then the phase II trial will continue to the targeted accrual of 25 patients.

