#### Treatment Stop Rule

A pause in study accrual will be implemented in the phase II portion of the trial after 10 patients have completed concurrent sorafenib plus conformal radiotherapy followed by surgical resection. Safety assessment will be made 6 weeks following resection of the 10th patient (9 – 13 weeks following completion of concurrent sorafenib and RT) to ensure that excess DLTs are not observed. The study will be **terminated for safety** (not lack of efficacy) if 4 of these 10 patients experience grade 3 adverse events or greater since this would represent an increase from the baseline rate of serious AEs expected from the standard combination therapy of preoperative radiation and surgical resection. This pause in accrual will allow us to review all safety data collected to date. If DLTs in excess of our stopping rule are not observed, then the phase II trial will continue to the targeted accrual of 25 patients.

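### The phase II stop rule triggers on grade 3 or greater adverse events, but its purpose and continuation condition are stated in DLTs, a narrower set under section 7.1

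*Protocol*

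**What the plan says.** The Treatment Stop Rule appears in Protocol section 7.1 and is repeated in 13.1.2. It pauses phase II accrual after 10 patients have completed sorafenib, radiotherapy and resection, with a safety assessment 6 weeks after the tenth resection. Three of its sentences name the event of interest:

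- Purpose: the assessment is made "to ensure that excess DLTs are not observed".
- Trigger: the study is terminated for safety "if 4 of these 10 patients experience grade 3 adverse events or greater". The reason given is that this would exceed the baseline rate of serious AEs with preoperative radiation and resection.
- Continuation: "If DLTs in excess of our stopping rule are not observed, then the phase II trial will continue" to its target of 25 patients.

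Section 7.1 defines DLT in the paragraph just before the rule. The hematologic part counts grade 4 anemia, grade 4 neutropenia lasting more than 7 days, grade 3-4 thrombocytopenia with clinically significant bleeding, and grade 4 thrombocytopenia lasting more than 5 days. Grade 3-4 non-hematologic toxicity counts, subject to listed exceptions that include "grade 3 diarrhea controlled with medication within 2 days" and grade 3 "hypertension that is adequately controlled with medication".

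**The concern.** The trigger and the continuation condition should be complements: if the rule is not met, the trial continues. Here they are written in different events, and one of those events is a term the protocol has just defined. Neither copy of the rule says that DLT has a wider meaning in phase II, and no separate DLT threshold is given for phase II. The second copy repeats the mismatch, so it does not resolve it.

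This is the only numeric go/no-go safety rule in phase II. The events that separate the two sets are plausible with this drug. Section 8.1 lists hypertension, diarrhea, nausea and hypophosphatemia as very common (10% or more) under sorafenib monotherapy, without giving grade 3 rates, and the DLT definition excepts each of them in whole or in part. If the count falls between the two readings, the choice of event decides whether the study stops, and it would be made with the results in view.

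**Working it through.** **Step 1: compare the event sets.** Every event in the DLT definition is grade 3 or 4, so every DLT patient is also a patient with a grade 3 or greater event. The converse fails. The following meet the trigger but are not DLTs under section 7.1:

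- isolated grade 3 anemia;
- grade 3 neutropenia, or grade 4 neutropenia of 7 days or less;
- grade 3 thrombocytopenia without significant bleeding;
- grade 3 hypertension controlled with medication;
- grade 3 diarrhea controlled within 2 days;
- grade 3-4 hypokalemia, hypophosphatemia, hypomagnesemia or hypocalcemia without hospitalization;
- nausea or vomiting that responds to anti-emetics, and short grade 3 neutropenic fever or encephalopathy.

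DLTs are therefore a strict subset of the trigger's events.

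**Step 2: construct a case.** Of 10 patients, 3 have a DLT and a fourth has only controlled grade 3 hypertension.

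- Grade 3 or greater count: 3 + 1 = 4. The trigger is met and the study is terminated.
- DLT count: 3. Read with the 7.1 definition and the rule's number 4, DLTs are not in excess and the study continues.

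The same conflict arises whenever at least 4 patients have grade 3 or greater events and at most 3 have DLTs.

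**Step 3: illustrate the size.** The protocol states no error rate for the rule, so there is no figure to reproduce, and it gives no grade 3 or DLT rates for the combination. The inputs are:

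- d, the DLT rate: 1/6 (assumed), and 0.33, the rate in the protocol's own definition, "The MTD is defined as the dose that produces dose limiting toxicity (DLT) in 33% of patients" (section 7.1);
- s, the share of patients with only non-DLT grade 3 or greater events: 0, 0.10 or 0.20 (assumed);
- n = 10 and a boundary of 4, from the rule.

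With X ~ Binomial(10, p), P(X ≥ 4) = 1 − [P(0) + P(1) + P(2) + P(3)]. Take p = d if only DLTs count and p = d + s if all grade 3 or greater events count. For d = 1/6 and s = 0.10:

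- DLTs only: 1 − (0.1615 + 0.3230 + 0.2907 + 0.1550) ≈ 0.070.
- All grade 3 or greater, p = 0.2667: 1 − (0.0450 + 0.1636 + 0.2676 + 0.2595) ≈ 0.264.

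The DLT count can never exceed the grade 3 or greater count. The probability of opposite decisions is therefore the difference of the two tails, here 0.264 − 0.070 ≈ 0.19.

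| d | s | d + s | P(≥4), DLTs only | P(≥4), all grade 3 or greater | P(opposite decisions) |
|---|---|---|---|---|---|
| 1/6 | 0 | 0.167 | 0.070 | 0.070 | 0 |
| 1/6 | 0.10 | 0.267 | 0.070 | 0.264 | 0.19 |
| 1/6 | 0.20 | 0.367 | 0.070 | 0.531 | 0.46 |
| 0.33 | 0 | 0.33 | 0.432 | 0.432 | 0 |
| 0.33 | 0.10 | 0.43 | 0.432 | 0.690 | 0.26 |
| 0.33 | 0.20 | 0.53 | 0.432 | 0.873 | 0.44 |

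**The case against.** The strongest reply is that only one sentence is an executable rule. The trigger has the count, the denominator and a mandatory action. The purpose sentence sets no threshold, and the continuation sentence refers back to the stopping rule, of which there is only one. The trigger's rationale is also a serious-AE rate, and the pause is meant for a review of all safety data. On this view DLT is loose shorthand and the trigger governs. That is the more natural reading, and it stands. A reader might infer that the protocol lays down two competing rules, or that nobody could tell when to stop. The text does not go that far, because continuing past a met trigger would mean letting the closing sentence override a mandatory one. What remains is that the shorthand reuses a defined term from the preceding paragraph, in two of the three sentences and in both copies.

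The probabilities depend on assumed shares. If no patient has only a non-DLT grade 3 event, the two readings agree. The figures illustrate the possible effect and do not estimate it.

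Two further inferences are tempting but unsupported:

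- Section 1.2 gives a 35% wound-complication rate with preoperative radiotherapy. At that rate P(at least 4 of 10) is 0.486, which might suggest that the broader trigger would stop the trial with no sorafenib effect. The figure does not separate the readings. Grade 3-4 wound toxicity is non-hematologic and falls under none of the DLT exceptions, so on the wording it counts either way, at least if judged treatment-related. Nor is 35% a grade 3 rate: no grade is stated, and section 10.4.2 counts a seroma aspiration as a major wound complication.
- The trigger says 4 rather than 4 or more. A rule that stops at 4 for excess toxicity plainly stops at 5, so this is no defect.

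**Conclusion.** The concern holds as an inconsistency of wording that can change a decision. The trigger counts grade 3 or greater adverse events, while the purpose and continuation sentences count DLTs, which are a strict subset. This rests on the text alone. The trigger is the natural operative sentence, so the likely practice is to stop on 4 patients with grade 3 or greater events, but the protocol should not leave that to interpretation.

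The size is unknown. Under the assumed rates, the chance that the two counts fall on opposite sides of the boundary runs from 0 (no patients with only non-DLT grade 3 events) to about 0.46. The sample size, the primary endpoint and the boundary of 4 in 10 are unaffected. The point is worth correcting but is not a major flaw.

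**What to change.** In both copies of the Treatment Stop Rule (sections 7.1 and 13.1.2), replace DLTs in the purpose and continuation sentences with *grade 3 or greater adverse events*, to match the trigger. If the sponsor intends only DLTs to count, put *DLT as defined in section 7.1* into the trigger instead and leave the other two sentences as they are. Either way, settle the event before the tenth patient's data are seen. The DLT definition itself stays unchanged.

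The cost is a wording amendment to one paragraph that appears twice, with no new data. The downside of keeping the present trigger is that it becomes explicit that controlled grade 3 events outside the DLT definition, such as medicated hypertension, can end the trial. The sponsor should choose knowing that.

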## 7.2 Sorafenib Dose Modification

7.2.1 General Considerations. According to the following dose level table, sorafenib dosing will be modified for adverse events that are at least in-part *attributable* to sorafenib according to the following sections.

| Dose Level | Sorafenib            |
|------------|----------------------|
| 0*         | 200 mg daily         |
| 1          | 200 mg twice daily   |
| 2          | 200mg am
400mg pm |
| 3          | 400 mg twice daily   |

\*Patients will be removed from protocol treatment if dose reduction below this level is indicated.

7.2.2 Dose Modifications for Sorafenib for Hand-Foot Skin Reaction

| Grade                                                                                                                                                                                              | Occurrence                 | Suggested Dose Modification                                                                                                                                                                                                                                                                                                                                                                                                                                                                                                                                                                                                                                                                                                                                                                                                                                |
|----------------------------------------------------------------------------------------------------------------------------------------------------------------------------------------------------|----------------------------|------------------------------------------------------------------------------------------------------------------------------------------------------------------------------------------------------------------------------------------------------------------------------------------------------------------------------------------------------------------------------------------------------------------------------------------------------------------------------------------------------------------------------------------------------------------------------------------------------------------------------------------------------------------------------------------------------------------------------------------------------------------------------------------------------------------------------------------------------------|
| Grade 1
Numbness, dysesthesia, paresthesia, tingling, painless swelling, erythema or discomfort of the hands or feet which does not disrupt the patient's normal activities                     | Any                        | Promptly institute supportive measures such as topical therapy for symptomatic relief and continue sorafenib treatment                                                                                                                                                                                                                                                                                                                                                                                                                                                                                                                                                                                                                                                                                                                                     |
| Grade 2
Painful erythema and swelling of the hands or feet and/or discomfort affecting the patient's normal activities                                                                          | First                      | 
Promptly institute supportive measures such as topical therapy for symptomatic relief and consider a decrease of sorafenib by one dose level for a minimum of 7 days and up to 28 days
 
 
• If toxicity resolves to grade 0–1 after dose reduction, increase sorafenib back to previous dose level
 
• If toxicity does not resolve to grade 0–1 despite dose reduction, interrupt sorafenib treatment for a minimum of 7 days and until toxicity has resolved to grade 0–1. 
 
▪ When resuming treatment after dose interruption, resume sorafenib at a one dose level reduction
 
▪ If toxicity is maintained at grade 0–1 at reduced dose for a minimum of 7 days and up to 28 days, increase back sorafenib to previous dose level
 
 
 
 |
|                                                                                                                                                                                                    | Second or Third occurrence | As for first occurrence. Upon resuming sorafenib, decrease dose by one dose level .
Decision whether to dose re-escalate should be based on clinical judgment and patient preference.                                                                                                                                                                                                                                                                                                                                                                                                                                                                                                                                                                                                                                                                   |
|                                                                                                                                                                                                    | Fourth occurrence          | Decision whether to discontinue sorafenib should be made based on clinical judgment and patient preference                                                                                                                                                                                                                                                                                                                                                                                                                                                                                                                                                                                                                                                                                                                                                 |
| Grade 3
Moist desquamation, ulceration, blistering or severe pain of the hands or feet, or severe discomfort that causes the patient to be unable to work or perform activities of daily living | First occurrence           | 
Institute supportive measures such as topical therapy for symptomatic relief and interrupt sorafenib treatment for a minimum of 7 days and until toxicity has resolved to grade 0–1
 
 
• When resuming treatment after dose interruption, decrease sorafenib by one dose level
 
• If toxicity is maintained at grade 0–1 at reduced dose for a minimum of 7 days and up to 28 days, increase by one dose level
 
                                                                                                                                                                                                                                                                                                                                                                               |
|                                                                                                                                                                                                    | Second occurrence          | As for first occurrence. Upon resuming sorafenib treatment, decrease dose by one dose level.
Decision whether to dose re-escalate should be made based on clinical judgment and patient preference.                                                                                                                                                                                                                                                                                                                                                                                                                                                                                                                                                                                                                                                     |
|                                                                                                                                                                                                    | Third occurrence           | Decision whether to discontinue sorafenib treatment should be made based on clinical judgement and patient preference.                                                                                                                                                                                                                                                                                                                                                                                                                                                                                                                                                                                                                                                                                                                                     |

